#### Baseline parameters

During their first visit to the emergency department or urgent care center, patients are assessed for eligibility. If informed consent is obtained, parameters regarding demographics, medical history, and injury are collected. Radiographic images and/or clinical pictures are taken as per local standard of care (routine) procedures. Demographic data, such as age, sex, height, weight, and ethnicity, are recorded. Medical history is documented in sufficient detail to calculate the Charlson Comorbidity Index, which has been designed and validated to classify prognostic comorbidity in longitudinal studies [11, 12]. Its prognostic accuracy has also been validated for a combined age-comorbidity index [13]. The recorded information includes the history of cardiovascular diseases, asthma, chronic lung disease, diabetes, renal disease, chronic liver disease, gastric or peptic ulcers, cancer, dementia, rheumatic or connective tissue disease, immunocompromised status [human immunodeficiency virus and/or others], and American Society of Anesthesiologists scores.

Information on medication history comprises the use of antibiotics, osteoporosis treatment, chronic use of analgesics and/or corticosteroids, and alcohol and drug intake. Information concerning the injury includes which side of the body the fracture is located on, high- or low-energy trauma, injury severity score, and fracture classification according to the AO/OTA fracture and dislocation classification [14]. Detailed information on additional fractures of the lower extremities both ipsilateral and contralateral will be collected. Furthermore, details of additional injuries will also be collected (e.g. cerebral, spine, thorax, abdomen, pelvis, upper extremity). Soft-tissue injury is to be classified according to Tscherne [15] for closed fractures and according to Gustilo-Anderson [16] and the OTA Open Fracture Classification [17] for open fractures. Concomitant fractures of the tibia or fibula are to be classified according to the AO/OTA fracture and dislocation classification [14].

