### Outcome measures

The data collected in this registry will include treatment details, clinical outcomes, PROs, and procedure- or implant-related AEs. Documentation of treatment details will comprise information about the time from injury to index surgery, duration of surgery, number of stages of the procedure, skin preparation, tourniquet use, details about debridement and irrigation, type of reduction/fixation method, specifics related to the fixation devices (e.g., material type, implant dimension*)*, intraoperative blood loss, as well as the use of local agents to promote bone healing. Moreover, information relating to the perioperative use of either prophylactic or curative systemic antibiotics and application of local antimicrobials will be documented and entered in the database. Furthermore, information pertaining to soft-tissue management will be recorded, such as timing and details of wound closure, soft-tissue coverage, and flap type. For concomitant fractures of the tibia or fibula, the treatment method will be documented. If further treatments are performed during the index surgery, these will also be captured.

Clinical outcome documentation will include time to bone healing/union, the presence of malalignment, malrotation or malunion, and the time to full weight bearing. Time to bone healing is defined as the time elapsed between definitive treatment and bony union. The healing status assessment will be based on a combination of clinical and radiological parameters, which will be judged by the treating surgeon. Clinically, healing will be rated as complete when the patient is able to walk without support in the absence of pain or tenderness at the fracture site. Radiologically, the modified RUST score [18] will be determined by scoring each cortex on the anteroposterior (AP) and lateral radiographs as 1 = no callus, 2 = callus present, 3 = bridging callus, and 4 = remodeled, fracture not visible. The modified RUST score is the sum of these and therefore has a value from 4 to 16.

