The pre-injury status concerning global health and physical function will be captured retrospectively at baseline and entered in the database. The *global health assessment* reflects an individual’s evaluation of their physical, mental, and social health. In this registry, a short form of 10 questions (v1.2) will be used. The *pain interference* questionnaire covers pain interference with physical, social, and recreational activities and will be documented with a short form of 8 questions (v1.0 – Pain Interference 8a). The *physical function (mobility)* questionnaire assesses the patients’ ability to perform various daily living activities, documented in a short form of 10 questions (v2.0 – Physical Function 10b). *Pain* will be documented on a numeric rating scale (NRS) from 0 to 10 for the injured leg, the knee of the injured leg, and the ankle of the injured leg. *Procedure- or implant-related adverse events*, i.e., complications, will only be documented for the injured tibia, but not for concomitant fractures in the fibular, malleolar, or other regions.

In addition to AEs entered via free text, some pre-defined complications will be captured. *Intraoperative pre-defined complications* include iatrogenic fracture, iatrogenic vessel damage, excessive bleeding, iatrogenic nerve damage, and intraoperative resuscitation. *Postoperative pre-defined complications* include compartment syndrome, FRI, nonunion, refracture/peri-implant fracture, secondary loss of reduction, secondary displacement or breakage of the fixation material, deep vein thrombosis, pulmonary embolism, ongoing pain medication, or inability to bear full weight 1 year after definitive treatment.

FRI will be diagnosed as defined in the recently published consensus definition [24] and subsequent update [25]. Additional contextual information will be collected for all AEs and comprises the start date of the event, its severity and seriousness, information about the related additional treatment(s), date of recovery, and the event’s outcome.

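### Ongoing pain medication at 1 year is a pre-defined complication with no new-onset condition, and clinical healing depends on unaided walking, so both can reflect causes other than the tibia

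*Protocol article*

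**What the plan says.** All places are in the Protocol article.

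- **Outcome measures, pre-defined postoperative complications.** The list ends with "ongoing pain medication, or inability to bear full weight 1 year after definitive treatment". I read the 1-year time point as applying to both items. Neither item carries a condition on cause, and the medication item carries none on prior use.
- **Outcome measures, scope of complications.** The registry collects "treatment details, clinical outcomes, PROs, and procedure- or implant-related AEs", and complications "will only be documented for the injured tibia, but not for concomitant fractures in the fibular, malleolar, or other regions".
- **Baseline parameters.** Medication history includes "chronic use of analgesics and/or corticosteroids". On other injuries: "Detailed information on additional fractures of the lower extremities both ipsilateral and contralateral will be collected", and "details of additional injuries will also be collected", with spine and pelvis among the examples. The exclusion criteria (Sample size estimation) remove neither group.
- **Outcome measures, healing.** Healing status combines clinical and radiological parameters as judged by the treating surgeon. Clinically, "healing will be rated as complete when the patient is able to walk without support", with no pain or tenderness at the fracture site. The modified RUST score is determined separately.
- **Outcome measures, time to full weight bearing.** This ends when the surgeon permits full load on the injured leg; use of a walking aid does not matter.
- **Statistical analyses.** Complication rates use the whole population as denominator, dropouts included, and carry 95% confidence intervals. Stratified summaries, including by treatment type, and possible multivariable analyses are foreseen.

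**The concern.** A complication is meant to be an event of the injured tibia linked to the procedure or implant. Taking analgesics at 1 year is a state of the whole patient. Someone who took them daily before the fracture for an unrelated condition will often still do so a year later, and the item as worded lets that be recorded as a complication. The registry holds the baseline record that would separate old from new use, but the definition does not draw on it.

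The walking criterion raises a related problem. A patient whose tibia has united but who needs a crutch for a contralateral or pelvic fracture does not meet it. Healing is a clinical outcome, not an adverse event, so the scope sentence for complications does not cover it.

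The Discussion gives relating treatment strategy to outcome as the registry's main purpose. The article also says that operative treatment follows fracture, soft-tissue and patient characteristics. If prior analgesic users or multiply injured patients are spread unevenly over treatments, part of any difference in these outcomes would not be about the tibia.

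**Working it through.** **No figure to reproduce.** The article gives no expected rate for either item, no prevalence of prior analgesic use or additional injuries, no dropout rate and no formal sample size calculation. The check is a comparison of the text, followed by an illustration on assumed inputs.

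**Text comparison**

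1. *Pain medication against the scope rule.* The rule names concomitant fractures in other regions. It does not mention medication that predates the injury. The same list contains deep vein thrombosis and pulmonary embolism, which are not located in the tibia, so a site cannot apply the tibia wording literally to every item. Other measures are localised: the pain rating scale refers to the injured leg and its knee and ankle. This item is not.
2. *Weight bearing against the scope rule.* Non-weight-bearing caused by another fracture falls under the rule's explicit exclusion, and the weight-bearing definition refers to the injured leg and accepts aids. This item is far better protected. What is missing is a statement that the rule applies to it.
3. *Healing against weight bearing.* One requires walking unaided, the other accepts an aid. They measure different things, so this is not a flat contradiction. Still, a patient can count as fully weight bearing and as clinically unhealed on the same day for a reason outside the tibia.

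**Illustration (all inputs assumed)**

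- p = true tibia-attributable rate at 1 year.
- q = share of the remaining patients who are positive for an unrelated reason and are counted.
- d = share lost before 1 year but kept in the denominator.

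Reported rate = (p + (1 − p)q)(1 − d). For p = 10%:

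| q | d = 0 | d = 10% | d = 20% | d = 30% |
|---|---|---|---|---|
| 0 | 10.0% | 9.0% | 8.0% | 7.0% |
| 5% | 14.5% | 13.05% | 11.6% | 10.15% |
| 10% | 19.0% | 17.1% | 15.2% | 13.3% |
| 15% | 23.5% | 21.15% | 18.8% | 16.45% |
| 20% | 28.0% | 25.2% | 22.4% | 19.6% |

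For example, q = 5% and d = 0 gives 0.10 + 0.90 × 0.05 = 0.145.

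*Precision for comparison.* The 95% half-width at N = 1000 and p = 10% is 1.96 × √(0.10 × 0.90 / 1000) = 1.9 points.

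*Net direction.* The two effects cancel at d = 1 − p/(p + (1 − p)q). For p = 10% and q = 5% this is 1 − 0.10/0.145 = 31%. For p = 20%, q = 5%, d = 30% the reported rate is 0.24 × 0.70 = 16.8%, below the true 20%.

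*Between groups.* With p = 10% in both groups, q = 5% in one and 15% in the other, the reported difference is 23.5 − 14.5 = 9.0 points, where the true difference is zero. Equal dropout of 30% shrinks this to 16.45 − 10.15 = 6.3 points but does not remove it.

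**The case against.** The strongest reply is that the scope rule already does the work. The list follows directly on the sentence restricting complications to the injured tibia, and relatedness to procedure or implant is stated twice. A careful site would not record analgesia for a pelvic fracture, or a leg unloaded because of another fracture. This largely stands for other injuries. It stands less well for medication that predates the injury, which the rule does not address, although the relatedness condition points the right way.

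A reader might infer that pre-injury users of a walking aid are counted as unable to bear full weight. The article does not support that, because its weight-bearing definition accepts aids and concerns the injured leg.

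A reader might also infer that the 1-year rates are inflated as a matter of fact. That is not shown either: no prevalences are given, and the whole-population denominator lowers the same rates. The denominator is, however, a separate effect that cannot be relied on to cancel this one.

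On healing, the surgeon's judgement combines clinical and radiological findings, which softens the walking criterion. The criterion remains a stated rule.

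Finally, the article condenses a fuller protocol that may define these items, and the registry is exploratory and already recruiting. That argues for a wording change using existing data. It does not remove the mismatch between the item and the scope rule as printed.

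**Conclusion.** The point holds in a limited form. The pain-medication item lacks a new-onset condition and is not reconciled with the scope rule, so pre-injury chronic users may be counted. This may raise the rate and may distort treatment comparisons. The clinical healing rule can label a united tibia as unhealed because of another injury, and its treatment of walking aids differs from that of the weight-bearing definition.

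The size is unknown. The 4.5 to 18 points added at p = 10% (q from 5% to 20%, d = 0) and the 9-point false difference rest wholly on assumed p and q. Equating q with the share of prior users further assumes that every one of them is still medicated at 1 year and recorded despite the relatedness rule; otherwise q is smaller. The figures show only that modest misattribution could exceed the 1.9-point half-width at N = 1000. They are not an estimate for this registry, and the net direction after dropouts is not fixed by the documents.

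**What to change.** 1. State that the restriction to the injured tibia and to procedure- or implant-related events applies to both 1-year items.
2. Count ongoing pain medication as a complication only in patients without chronic analgesic use at baseline, and show baseline users separately. Under the illustration with d = 0 and c the share of prior users, the restricted rate is (1 − c) × 10% / (1 − c) = 10% whatever c is.
3. Report inability to bear full weight and clinical healing overall and by presence of additional lower-limb, pelvic or spinal injuries.
4. Report radiological union from the modified RUST score separately from the clinical walking criterion.

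These are changes to wording and tables. They need no new form field, provided the baseline form lets analgesics be told apart from corticosteroids, which the article names together. The cost is a slightly smaller denominator for the restricted rates. If 15% of 1000 patients were prior users, 850 would remain and the half-width at 10% would be 1.96 × √(0.09 / 850) = 2.0 points instead of 1.9. Restriction also leaves out baseline users whose tibia adds to their need for medication, which is why they should be shown separately.

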### Data collection and management

Data handling and protection will be conducted according to the ISO 14155 guidelines, ICH-GCP, and applicable regulations. An electronic case report form (eCRF) has been designed in REDCap Cloud (https://www.redcapcloud.com/) to accommodate the registry’s specific features.

The REDCap Cloud is browser-based, metadata-driven, state-of-the-art electronic data capture software. Access to the eCRF is password-protected, and specific functions are assigned. The eCRF is to be completed promptly after a patient’s visit (i.e., 14 days after the occurrence of a documentable event).

During the site initiation visit and prior to recruiting the first patient, the research team at each site underwent a defined training program that includes explanations on inclusion and exclusion criteria, registry procedures, how to use the eCRF, and general aspects of ISO 14155 and GCP. Monitoring visits are to be performed on-site or remotely (via a web conference) as frequently as required to guarantee the completeness and accuracy of the information in the eCRF. Source data and any other essential documents must be archived according to the study site’s legal requirements. Clinical study data (i.e., eCRF) and essential documents will be archived by the sponsor according to the legal requirements.

### Premature termination

Due to the nature of the registry, no stopping rules have been defined. All treatments will be per standard of care, and no additional or investigational medical device or medication will be administered during the investigation. Patient participation in the study may end prematurely for one of the following reasons:
The patient withdraws informed consentScreening failure (patient not meeting the eligibility criteria)Investigator’s discretion (e.g., patient noncompliance with the registry plan)Sponsor’s decisionUnknown/lost to FUDeath

In the case of premature termination, detailed information explaining the circumstances leading to termination will be obtained and recorded in the eCRF.

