#### Interventions and study procedures

Patients will undergo fracture fixation using osteosynthesis, including single- or multiple-staged procedures (e.g., initial external fixation with later conversion to internal fixation). The operative treatment for TSFs in adults mainly depends on the fracture characteristics and extent of the soft tissue damage and is to be performed according to the standard (routine) care procedures based on the individual clinician’s judgment and patient characteristics. Neither specific treatment nor specific time points for FU visits are dictated for registry purposes.

Registry-related assessments will include radiographic evaluations, performed by the treating surgeon at the treatment visit and at defined time points after treatment, following each site’s standard (routine) visit schedule for up to 36 months. Radiographic images and/or clinical pictures will be stored to enable future ad-hoc analysis after de-identification. If patients are unable to attend the last planned FU visit, they will be contacted by e-mail or phone to document the final outcomes, especially patient-reported outcomes (PROs) and complications not previously captured. The planned registry schedule is displayed in Table 2 over the 36-months FU visit period.

**Table 2 Tab2:** Registry schedule for the Fracture-Related Outcome Study for operatively treated Tibia shaft fractures (F.R.O.S.T.)

	Baseline	Treatment	Post-treatment visit 1^a^	Post-treatment visit 2^a^	Post-treatment visit 3^a^	Additional Post-treatment visit(s)^a^
	–	Day 0	6 weeks (target 42 days: range 14 to 105)	6 months (target 183 days; range 106 to 260)	12 months (target 365 days, range 261 to 456)	Up to 36 months
Eligibility	X					
Patient information/consent	X^b^					
Demographics	X					
Medical history and pre-treatment values	X					
Injury(s) details	X					
Treatment details		X^c^				
Clinical outcome(s)			X	X	X	X
Patient-reported outcome(s)						
PROMIS: Global Health	X		X	X	X	X
PROMIS: Physical Function	X		X	X	X	X
PROMIS: Pain Interference			X	X	X	X
Pain numeric rating scale (NRS)			X	X	X	X
Complications			X	X	X	X
Images and/or other clinical pictures	X^d^	X^d^	X^d^	X^d^	X^d^	X^d^

^a^ If a patient does not visit at the specified time point, the visits will be assigned according to the specified rules. Additional postoperative visits may take place up to 36 months after day 0

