### Statistical analyses

As the registry aims are mainly descriptive and exploratory, patient characteristics and outcomes recorded at the standard of care scheduled FU assessments will be presented using simple summary statistics. Categorical variables will be summarized using the frequency and percentage for each category. Continuous variables will be summarized using the mean, standard deviation, median, interquartile range, and the minimum and maximum values. Additionally, summary statistics will be presented and stratified to clinically relevant categories, including the type of treatment received. Complications will be reported at both the patient and AE levels. Multiple events of the same type will be combined for each patient. Upon calculating complication rates, the denominator will be the total population size, irrespective of dropouts during FU. All complication rates will be presented with 95% confidence intervals. In addition to overall rates, complications will be presented according to categories for various relevant parameters, such as “action taken” (none/operative/nonoperative) or “outcome” (in progress/without persistent damage/with persistent damage/death). Patients with more than one event of the same type will be presented according to the most severe category.

To identify risk factors and evaluate specific research questions, it is planned to perform further appropriate statistics (e.g., multivariable analyses) if the volume and quantity of the collected data allows this. Enrolled patients who withdraw from the study FU for any reason (withdrawal of consent, death, loss to FU, etc.) will be included in the analysis until the time at which they withdrew.

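### Noncompliance as a ground for ending participation permits avoidable loss of follow-up, and the fixed denominator then counts later complications as non-events

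*Protocol article*

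**What the plan says.** Five statements in the protocol article bear on this point.

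- **Premature termination.** Participation may end for several listed reasons. Investigator's discretion is one, with "patient noncompliance with the registry plan" as its only example. Withdrawal of consent and loss to follow-up are separate entries. When participation ends, the circumstances are to be recorded in the eCRF. A final outcome contact is not mentioned.
- **Interventions and study procedures.** "Neither specific treatment nor specific time points for FU visits are dictated for registry purposes". The footnote to Table 2 adds: "If a patient does not visit at the specified time point, the visits will be assigned according to the specified rules".
- **Same section, on non-attendance.** "If patients are unable to attend the last planned FU visit, they will be contacted by e-mail or phone to document the final outcomes". This contact also covers complications not yet captured. Outcome measures describes the same remote route for planned follow-up visits in general.
- **Statistical analyses, on patients who leave.** Patients who leave follow-up for any reason "will be included in the analysis until the time at which they withdrew".
- **Statistical analyses, on complication rates.** "the denominator will be the total population size, irrespective of dropouts during FU".

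**The concern.** In a registry that follows local routine care, a patient can fail to comply with little beyond attendance and questionnaires. For off-schedule visits the article has an assignment rule, and for patients unable to attend it has remote contact. The termination section nevertheless offers the investigator a different route for a patient who does not cooperate fully, which is to end participation.

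Because withdrawal of consent and loss to follow-up are listed separately, this ground reaches patients who still consent and may still be reachable. Data lost this way are lost by a choice within the study's control. The article does not define noncompliance, so sites can apply the ground differently.

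Two things are at stake. The first is the complication rates, because several predefined complications can arise or be judged late: fracture-related infection, nonunion, and inability to bear full weight at one year. The second is comparison. The Discussion gives the association between treatment strategies and outcomes as the main purpose. If sites differ both in treatment and in how readily they end participation, under-counting would differ between the strategies compared.

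**Working it through.** **Step 1: the rules applied to one patient.** Take a patient who misses routine visits and has not withdrawn consent.

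| Rule | Consequence |
|---|---|
| Table 2 footnote | Off-schedule visits are assigned to a time point by rule |
| Interventions and study procedures; Outcome measures | If unable to attend, the patient is contacted by e-mail or phone and outcomes are captured |
| Premature termination | The investigator may end participation; only the circumstances must be recorded |
| Statistical analyses (patients who leave) | Data are used until exit |
| Statistical analyses (denominator) | The patient stays in the denominator |

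If the investigator takes the third route, a complication after exit is absent from the numerator while the patient remains in the denominator.

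**Step 2: formula.** The article states no figure to reproduce: it has no formal sample size calculation and no assumed dropout or removal rate. Let d be the share removed on this ground, r₀ the risk in the other patients, r₁ the risk in removed patients, and m the share of removed patients' events that fall after exit and go uncaptured.

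- True rate = (1 − d)·r₀ + d·r₁
- Observed rate = (1 − d)·r₀ + d·r₁·(1 − m)
- Bias = observed − true = −d·r₁·m

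The bias is never positive, whatever r₁ is. At equal risk (r₁ = r₀) the relative bias is −d·m.

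**Step 3: inputs.**

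- N = 1000: planned enrolment (Sample size estimation).
- r₀ = 10%: assumption. It lies inside the 3–17% nonunion range in Background.
- r₁ = 10% (equal risk), 20%, or 27.5%: assumptions. The last is the midpoint of the 25–30% infection range in Background for complex open fractures.
- d = 2%, 5%, 10% and m = 0.5 to 1: assumptions.

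**Step 4: results.** Percentage points by which the observed rate is too low, for m = 0.5 to m = 1:

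| d | r₁ = 10% | r₁ = 20% | r₁ = 27.5% |
|---|---|---|---|
| 2% | 0.10–0.20 | 0.20–0.40 | 0.28–0.55 |
| 5% | 0.25–0.50 | 0.50–1.00 | 0.69–1.38 |
| 10% | 0.50–1.00 | 1.00–2.00 | 1.38–2.75 |

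Worked example at equal risk with d = 5%: 50 patients are removed and 5 events are expected among them. If all 5 are missed, the observed rate is 95/1000 = 9.5% instead of 10%. If half are missed, it is 97.5/1000 = 9.75%.

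**Step 5: comparison with sampling error.** The 95% half-width at a rate of 10% is 1.96 × √(0.10 × 0.90 / 1000) = 1.86 points. Across all the scenarios it runs from 1.77 to 1.89.

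**The case against.** The strongest reply is that the rules do not collide. The termination clause is permissive, the remote contact is for patients unable to attend, and inability is not noncompliance. Patients also have registry tasks, namely the PROMIS questionnaires and pain scales, and Table 2 gives target windows, so noncompliance has some content. The article is condensed, and the full protocol may define the term. The aims are mainly descriptive, and the illustrated bias is mostly smaller than the confidence interval half-width.

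Much of this stands. The passages are in tension but are not opposite instructions. The lack of a definition in a condensed article is not the fault raised here. The point is that the article expressly names this ground, and using it loses outcomes that the article's own procedure could capture.

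Several stronger readings are tempting, and the document does not support them:

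- **Higher-risk patients are the ones dropped.** Nothing links noncompliance to risk. It is plausible, but the downward bias does not need it.
- **The direction of bias varies by site.** For complication rates, missed events with a fixed denominator can only lower the rate. Only the size can vary by site. For patient-reported outcomes the direction is unknown.
- **Patients are removed from the analysis.** They leave follow-up only. Recruitment defines the follow-up population by consent, eligibility and commenced treatment. Data up to exit are kept and the circumstances are recorded.
- **The final contact is explicitly denied.** No sentence says so. Its loss is inferred from participation having ended.

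**Conclusion.** The concern holds in a limited form. The noncompliance ground sits badly with a registry that imposes no treatment or visit times and has a remote route to outcomes. It permits avoidable loss of follow-up in patients who have not withdrawn consent, to an extent that can differ by site. With the stated denominator, that loss lowers complication rates even when risk is average.

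At equal risk the illustrated shortfall is 0.1–1.0 points on a 10% rate, below the half-width of about 1.9 points. It approaches or exceeds that half-width only if removal is both frequent and selective: at 10% removed, 1.38–2.75 points when the removed patients' risk is 27.5%. Unlike sampling error, the bias does not shrink with more patients. All sizes rest on assumed removal rates, risks and shares of events missed. They also assume that removed patients receive no final contact. The point merits correction because the remedy is nearly free, not because the expected bias is large.

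**What to change.** In Premature termination, delete noncompliance as an example of investigator's discretion. Add that a patient who misses visits or questionnaires but has not withdrawn consent stays in follow-up and receives the e-mail or phone final-outcome contact already described in Interventions and study procedures. Align the eCRF list of reasons for ending participation with this. The other reasons, including the sponsor's decision and investigator's discretion on other grounds, can stay.

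The cost is a wording change and a little more contact work for sites. It will not recover patients who truly cannot be reached. For them the fixed denominator still counts unobserved complications as non-events.
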